### Study design

This study is a randomised, participant and investigator-masked, inactive placebo-controlled parallel-group trial with 80 participants. Participants will be allocated into parallel groups in blocks of ten in a 1:1 ratio. Given the early stage of this field, an exploratory framework has been chosen. The study drug or placebo will be self-administered by participants from 1-ml oral syringes containing 10 μg of LSD or placebo (see the “Drug preparation and administration” section). Visits will take place at research facilities in the Faculty of Medical and Health Sciences on the Grafton Campus of Auckland University in New Zealand.

At a screening visit, volunteers will give informed consent, be checked for eligibility, and will be approved for inclusion by a study psychiatrist. Written informed consent will be obtained by members of the study team from the participants through the process outlined below. A participant information sheet (PIS) and informed consent form (see Additional File 1) will be supplied to prospective participants prior to their attendance at the screening visit, with adequate time to seek independent advice, for example, from a lawyer, general practitioner (GP), and relevant family members. These forms contain information on the nature of the trial, what involvement will entail for the participant, the implications and constraints of the protocol, the known side effects, and any risks involved in taking part. Participants will have the opportunity to ask questions of the study investigators prior to and again during the screening visit, and their verbal understanding of the information will be confirmed prior to giving written informed consent. Continuing eligibility and verbal consent will be reconfirmed at every study visit.

Following acceptance to the trial, participants will return for a second visit to collect baseline measures (day − 6; see Fig. 1). The following evening, participants will receive a text message with a link to complete a questionnaire of visual analogue scale (VAS) ratings every day until the final study visit (day 43). One week later (day 1), participants will return to the lab to receive a single dose of their first allocated intervention and be monitored for 6 h before being discharged. Blood will be drawn prior to drug administration and at 30, 60, 120, 240, and 360 min after administration. Subjective drug effect measures will also be collected at these time points. EEG measures will be taken at ~ 150 min after administration and creativity measures at ~ 260 min. Participants will be discharged with four additional doses and will then self-administer oral syringes sublingually every third morning on 12 occasions and fourth morning on one occasion (days 4, 7, 10, 13, 16, 19, 22, 25, 28, 31, 34, 37, 41). Participants will make a brief re-supply/health check visit on days 14 and 26 and will receive 4 and 5 additional doses, respectively, on these dates. On day 43, all baseline measures will be repeated, as well as a qualitative interview. Brief follow-up telephone interviews will be conducted at 1 and 3 months.

**Fig. 1 Fig1:**
[figure not shown]
Schedule of enrolment, interventions, and assessments

Participants will be withdrawn from the trial and the intervention will be immediately ceased if the participant requests it, one of the exclusion criteria above is identified or violated, there is not adequate dose compliance, they experience a serious adverse event, they experience a persistent non-serious adverse event which interferes with their daily functioning, and any other condition emerges which is judged by the study team as likely to impact on the ability of the participant to complete the trial. Decisions about withdrawing participants will be made with the advice of study clinicians.

### Outcomes

The timeline of assessments is outlined in Fig. 1, with summaries of primary measures and secondary measures in Table 3. Questionnaires, including the primary personality measures (BFI-2 and MODTAS), will be self-administered (see the “Data collection and management” section) at the baseline and after the treatment period on day 43. BFI-2 measures five personality dimensions; however, only open-mindedness will be treated as a primary outcome, with the others being assessed as secondary outcomes. EEG and creativity measures will be repeated at baseline, in the acute phase of the first dose on day 1, and on day 43. fMRI will be repeated at baseline and day 43 only.

**Table 3 Tab3:** Primary and secondary measures

Measure	Domain	Scale
Primary measures		
Alternate Uses Test (AUT) [35]	Creativity: divergent thinking	3 items; participants are given the name of a household item and are given 2 min to produce possible uses; responses are marked for fluency (number of responses), flexibility (number of different categories of responses), elaboration (number of elaborative details), and originality (uniqueness of response).
Big Five Inventory-2 (BFI-2) [50]	Personality: open-mindedness, agreeableness, conscientiousness, extraversion, negative emotionality	60 items on a 5-point scale (1–5) from “disagree strongly” to “agree strongly” with 5 scales reported as the mean response. Open-mindedness scale evaluated as a primary measure and all others as secondary measures.
Visual Long-Term Potentiation Paradigm (EEG LTP) [55]	Plasticity: Hebbian plasticity	Participants are presented with visual stimuli which is “tetanised” with high-frequency stimulation, assessed as the amplitude of visual-evoked ERP response to tetanised stimuli vs non-tetanised stimuli.
Roving Mismatch Negativity Paradigm (EEG MMN) [56]	Plasticity: predictive coding	Participants are presented with a series of tones followed by a series of deviant tones, assessed as the amplitude of auditory-evoked ERP response to deviant tone and rate of subsequent habituation to tone.
Modified Tellegen Absorption Scale (MODTAS) [28, 51]	Personality: absorption	34 items rated on a 5-point scale (0–4) reported as the sum of scores (0–136).
Remote Associates Task (RAT) [52]	Creativity: convergent thinking	20 items; participants are given 3 words and need to produce a word that all 3 have in common, assessed as number correct and number attempted.
Resting-State fMRI	Connectivity	9-min continual recording on 3-T Siemens scanner with a 32-channel head coil.
Secondary measures		
5-Dimensional Altered States of Consciousness Questionnaire (5D-ASC) [57, 58]	Drug effects: psychological	91 items rated on VAS (1–100) with 5 scales and 11 subscales reported as % of the maximum score.
Adverse events	Unwanted health effects	Participants are asked daily to report any “unpleasant health issues” and to rate them as mild, moderate, or serious.
Consensual Assessment Technique (CAT) [59]	Creativity: non-specific	Participants are given 15 min to complete a paper collage; the result is rated by independent assessors on VAS (0–100) from low to high on (1) creativity and (2) technical goodness, reported as mean rater response.
Detail and Flexibility Questionnaire (DFlex) [60]	Attention to detail and cognitive rigidity	24 items on a 6-point scale (1–6) with 2 subscales reported as the sum of scores (total 24–144; subscales 12–72).
Daily questionnaire	Mood: well, sad, happy, stressed, creative, anxious, focused, tired, calm, connected, angry, energy, irritable, motivated, craving	15 items rated on VAS (0–100) reported as individual scores.
Depression, Anxiety, and Stress Scale (DASS) [61]	Mood: depression, anxiety, stress	42 items on a 4-point scale (0–3) with 3 subscales reported as the sum of scores (0–42).
Drug Effects Visual Analogue Scale (VAS)	Drug effects: psychological	16 items rated on VAS (0–100) reported as individual and mean scores.
Electrocardiogram (ECG)	Drug effects: physiological	QT interval, heart rate variability.
Everyday Problem-Solving Questionnaire	Creativity: problem solving	4 items rated on a VAS (0–100) reported as individual and mean scores.
Expectancy questionnaire	Expectancy	18 items rated on VAS (0–100; see Table 4).
Five Facets of Mindfulness Questionnaire (FFMQ) [62]	Mindfulness: observe, act with awareness, non-judgement, describe, non-reacting	39 items rated on a 5-point scale (1–5) with 5 subscales reported as the mean of scores.
Fitbit Charge 4, Activity and Sleep Tracker, manufactured by Fitbit, San Francisco, CA, USA	Drug effects: physiological	Activity reported as steps per day and sleep reported as minutes asleep per day.
Genetic biomarkers	Genetic	BDNF Val66Met.
Inflammatory cytokines	Immune modulation	Plasma concentration of inflammatory cytokines analysed reported in pg/ml.
NIH Toolbox Picture Vocabulary Test, Flanker Inhibitory Control and Attention Test, Picture Sequence Memory Test, List Sorting Working Memory Test, Dimensional Change Card Sort Test, Pattern Comparison Processing Speed Test [63]	Cognition: language, attention, executive function, episodic memory, working memory, processing speed	Reported as individual scores and NIH Fluid Cognition Composite Score Uncorrected Standard Score [64].
NIH Toolbox Anger-Affect, Anger-Hostility, Anger-Physical Aggression, Positive Affect, General Life Satisfaction, Meaning and Purpose, Emotional Support, Instrumental Support, Loneliness, Friendship, Perceived Hostility, Perceived Rejection, Self-Efficacy [65]	Mood: anger, positive affect, general life satisfaction, meaning and purpose, social support, companionship, social distress, self-efficacy	Reported as individual scores and NIH Psychological Well-being Summary, Social Satisfaction Summary [64].
Pharmacokinetic/pharmacodynamic (PKPD) measures	Drug metabolism	Plasma concentration of drug in pg/ml.
Peripheral mononuclear blood cell (PMBC) biomarkers	Physiology	5HT2A receptor mRNA expression in PMBC cells.
Profile of Mood States (POMS) [66]	Mood: fatigue, tension, depression, anger, vigour, confusion	65 items on a 5-point scale (0–4) with 6 subscales reported as the sum of scores.
Perceived Stress Scale (PSS) [67]	Mood: stress	10 items on a 5-point scale (0–5) reported as the sum of scores.
Self-Assessment Manikins (SAM) [68]	Drug effects: valence, arousal, dominance	3 items on a 9-point scale (1–9) reported as individual scores.
Semi-structured audio interview	Open-ended	~ 30-min interview with open-ended questions about the experience of microdosing trial for qualitative analysis.
Subject release interview	Open-ended	Brief discussion of participant’s experience of first dose and assessment of safety to discharge.
State of Surrender (SoS) [69]	Mindset: surrender	10 items on a 6-point scale (1–6) reported as the mean of scores.
State of Preoccupation (SoP) [69]	Mindset: preoccupation	4 items on a 6-point scale (1–6) reported as the mean of scores.
Vital signs	Physiology	Systolic and diastolic blood pressure in mmHg and heart rate in bpm.

### Participant recruitment

Advertisements will be placed on local noticeboards, on social media, and distributed via university mailing lists. Potential participants will be instructed to contact the study team via email. Participants will be compensated with $120 in supermarket vouchers for participating in the trial.

### Randomisation, masking, and code breaking

Eligible participants will be enrolled by a masked member of the study team. A biostatistician will perform the allocation of participants to either the active intervention or placebo (in blocks of ten at a 1:1 ratio) based on a computer-generated random sequence. Only the statistician and pharmacist members of the research team and the drug manufacturer will know the identity of the drugs to be administered (see the “Drug preparation and administration” section). Unmasked team members will not interact with study participants and will not be present during any drug administration sessions. The study team will be unmasked at the completion of each randomisation block; however, the participants will not be unmasked until the full completion of the trial.

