### Data and safety monitoring

The Trial Steering Committee (TSC) will provide overall supervision of the trial. The TSC will comprise all of the authors listed. In particular, the TSC will collaboratively develop and approve the final protocol; oversee the progress of the trial, adherence to the protocol, participant safety, and consideration of new information; and be responsible for publication and dissemination. The TSC must be in full agreement prior to submission of the final protocol. The TSC will take responsibility for the following, for which at least 50% of the investigators including the principal investigator (PI) must be in agreement: major decisions such as a need to change the protocol for any reason, monitoring and supervising the progress of the trial, and reviewing relevant information from other sources.

The study will be overseen by a DSMC provided by the Health Research Council of New Zealand (HRC), the primary funders of this study. The DMSC consists of two biostatisticians, several clinicians, and an ethicist. Reports will be submitted to the DMSC every 6 months for review of trial progress and conduct. Protocol amendments will be submitted to the DSMC, as well as Medsafe and the approving Ethics Committee.

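### The study team is unmasked after every block of ten while the trial runs on, which conflicts with the investigator-masked design and lets knowledge of earlier results by arm reach later participants and decisions

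*Protocol article*

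**What the plan says.** The Study design section calls this a "randomised, participant and investigator-masked, inactive placebo-controlled parallel-group trial" with 80 participants, and adds: "Participants will be allocated into parallel groups in blocks of ten in a 1:1 ratio".

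The section on randomisation, masking and code breaking contains four statements that matter here:

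- On who holds the allocation: "Only the statistician and pharmacist members of the research team and the drug manufacturer will know the identity of the drugs to be administered".
- Unmasked team members are to have no interaction with participants and are to stay away from dosing sessions.
- On the team: "The study team will be unmasked at the completion of each randomisation block".
- On participants: "the participants will not be unmasked until the full completion of the trial".

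The document does not define completion of a block and gives no reason for unmasking block by block.

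Contact with participants continues after the day-43 visit: "Brief follow-up telephone interviews will be conducted at 1 and 3 months" (Study design). Under Data and safety monitoring, "The TSC will comprise all of the authors listed", and that committee decides on protocol changes.

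**The concern.** The team that recruits, doses, tests and interviews is told the arms of each finished block while later blocks are still being run. Three things are at stake.

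- **Conduct of later blocks.** Staff watch each participant for 6 hours after the first dose, collect repeated drug-effect ratings and review daily adverse event reports. Setting these against revealed arms teaches staff what an active dose looks like and can sharpen their guesses about later participants. They can also convey expectancy. The Discussion keeps participants masked to the end so that they cannot tell associates in the trial which arm produced their experience. That closes the route on the participant side only.
- **Decisions.** The steering committee, made up of all the authors, could consider protocol changes while knowing accumulating results by arm.
- **Unfinished work on opened blocks.** Telephone follow-up remains, and so does any scoring or processing not yet done.

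Expectancy and unmasking are the confounders this trial stresses most, so a rule that weakens masking on the staff side is costly here.

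**Working it through.** There is no stated figure to reproduce. The check sets the statements side by side and then works out what is still open at each unmasking.

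**1. Consistency.** Once the first block is opened, the study team is unmasked for ten people. The same section says unmasked team members do not interact with participants. Yet later blocks still have to be run, and the 1- and 3-month calls may still be due. If the same staff continue, the no-contact rule fails. If they may not, nobody is named to replace them.

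**2. Number of unmaskings.** Blocks = 80 / 10 = 8, so up to seven openings precede completion of the eighth. At the first opening, 80 − 10 = 70 participants belong to blocks not yet complete.

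**3. What is still open within a block.** Recruitment starts on 12 April 2021 and the trial is due to end in mid-2022 (Trial status). Assumptions: an end date of 30 June 2022, even accrual, calls 30 and 91 days after day 43, and 49 days from baseline (day −6) to day 43. The span is 444 days.

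- If the last day-43 visit falls at the end: gap between participants = (444 − 49) / 79 = 5.0 days.
- If the last 3-month call falls at the end: gap = (444 − 49 − 91) / 79 = 3.8 days.

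The participant in position j of a block is (10 − j) × gap days ahead of the last one.

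*Completion = last participant's day 43.* A call falls after unmasking if (10 − j) × gap is below 30 (one-month) or 91 (three-month).

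*Completion = last participant's first dose.* A participant is still short of day 43 if (10 − j) × gap is below 42.

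| Gap (days) | One-month calls after unmasking | Three-month calls after unmasking | Before day 43 at unmasking (first-dose reading) |
|---|---|---|---|
| 3 | 10 of 10 | 10 of 10 | 10 of 10 |
| 3.8 | 8 of 10 | 10 of 10 | 10 of 10 |
| 5 | 6 of 10 | 10 of 10 | 9 of 10 |
| 7 | 5 of 10 | 10 of 10 | 6 of 10 |
| 10 | 3 of 10 | 10 of 10 | 5 of 10 |
| 14 | 3 of 10 | 7 of 10 | 3 of 10 |

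**4. Overlap with the next block.** On the day-43 reading, participants of the next block already dosed when a block is opened = 42 / gap, rounded down: 8 at a gap of 5.0 days and 10 at 3.8. Staff would learn one block's arms while the next is on treatment.

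**5. The most protective reading.** Suppose completion includes the last 3-month call. A block takes 10 × gap = 50 or 38 days. Since 91 / 50 = 1.8 and 91 / 38 = 2.4, opening lags by two or three blocks. Then six or five blocks are open before the last participant's day 43. The calls are protected, but later conduct and protocol decisions are not.

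**The case against.** Much of the case on the other side stands.

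- **Later allocations stay hidden.** A reader might infer from 70 / 80 = 87.5% known allocations that masking is almost entirely lost before the last block is assessed. The document does not support that. The 70 are in finished blocks, and opening them reveals nothing about the eighth. On the day-43 reading, each participant's treatment and day-43 visit take place with that participant's arm unknown to the team.
- **The statement on who knows the allocation is prospective.** It concerns drugs still to be given, so it is compatible with opening a block after dosing. The sharper conflict is with the no-contact rule and the investigator-masked label.
- **Scoring.** A reader might infer that the team marks the Alternate Uses Test and cleans EEG and fMRI data knowing the arm. The article does not say who does this or when, and a condensed article may leave that to fuller documents. It is an open risk, not a stated fact. The BFI-2 and MODTAS are self-administered, the Remote Associates Task is counted as correct and attempted, and the collage task has independent assessors.
- **Withdrawals and the extra block.** Withdrawal judgements arise during treatment, before the participant's own block is opened on the day-43 reading. The extra block follows a count of more than ten dropouts, not results by arm. Neither adds much.
- **Outside checks.** Amendments go to the DSMC, Medsafe and the ethics committee, which partly limits the steering committee.
- **Late calls.** They are brief and carry no primary outcome.
- **Purpose.** No rationale is given for early unmasking, but that does not show that none exists.

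The conflict over contact with participants remains, as does team and committee knowledge of earlier results by arm.

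**Conclusion.** The concern holds as an explicit rule that conflicts with the stated design; it is not a missing detail. The team can be unmasked up to seven times before the eighth block completes. The exposure is to conduct of later blocks, to protocol decisions and, depending on the meaning of completion, to late calls (6 to 8 of 10 at one month and 10 of 10 at three months under the planned timeline) or to day-43 primary outcomes (9 to 10 of 10 participants on the first-dose reading). These counts rest on even accrual and an assumed end date; the table shows how they move with other gaps.

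Allocation concealment for later blocks is not directly broken, and unmasked scoring is not established. The size of any bias cannot be computed from the document. The point should be settled before the first block is opened, because the knowledge cannot be withdrawn afterwards.

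**What to change.** Replace the sentence on block-wise unmasking. State that all staff with participant contact, outcome scorers, EEG and fMRI processors, and the steering committee stay masked until three conditions are met: the last participant's last follow-up is done, scoring and preprocessing are complete, and the database is locked. The statistician and pharmacist, who are already unmasked, hold the codes and prepare the by-arm tables for the DSMC. Emergency unmasking stays as written.

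The cost is one sentence in the protocol and a wait until database lock before the team sees allocations. Sample size, alpha and power do not change.

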### Drug preparation and administration

The study drug and placebo doses will be prepared by Biomed Ltd. (Auckland, New Zealand) to Good Manufacturing Practice (GMP) standards. The manufacturer will be supplied with randomisation codes for labelling each packet of five syringes by the study pharmacist. The study pharmacist will label and dispense the packets for each participant via a masked member of the study team. The study pharmacist will maintain an unmasked database of all participants. Emergency unmasking will be performed by the study pharmacist or their delegate in the case of a SAE or in any other scenario deemed necessary by the study clinicians.

### Strategies to improve adherence

Mobile Directly Observed Therapy (MDOT) will be used to monitor adherence to the home-dosing protocol. MDOT has been used recently in a variety of medication contexts including treatment of tuberculosis, HIV, opioid dependence, and asthma inhaler use [70]. Each dosing morning, participants will receive a text reminder with a link to upload a video of themselves self-administering. Participants will use their mobile phones to video themselves stating the date, displaying the sealed and labelled dose, then emptying the syringe into their mouth, holding their mouth closed for 30 s, and then providing a clear view of their empty mouth. Videos will be uploaded to a secure server to be checked by the study team and deleted immediately after viewing. Participants who fail to record the video correctly will be reinstructed, and those that fail to record repeatedly will be eliminated from the trial.

### Relevant concomitant care and post-trial care

Participants will receive care as normal from their GP during the trial and will be given guidelines of preferred treatments for any non-exclusionary health issues that occur within the trial. Long-term harm to participants is considered highly unlikely; however, participants will be able to apply for compensation for any injury sustained during the trial under the New Zealand Accident Compensation Corporation (ACC) scheme.

### Statistical analyses and power calculations

Given the novelty of the study, there are no effect sizes on which to base power calculations. The following power sensitivity calculations were performed in G*Power 3.1 [71] using *α* = 0.05, (1-*β*) = 0.8. For independent sample *t* tests where *n* = 80, our trial will be sensitive to the effects where Cohen’s *d* = 0.56. For linear regressions, *r =* 0.37 with *n* = 40 (single group) and *r* = 0.27 with *n* = 80 (combined groups). Dropouts are anticipated; however, due to the novelty of the protocol, the rate cannot be estimated. Dropouts and other instances of missing data will be accounted for in the analysis (see the “Sub-group data analysis and handling missing data” section). In the event that there are more than ten dropouts, an extra randomisation block of participants will be added to the study and the data added to per-protocol analyses.

Questionnaires and creativity tasks will be assessed with linear mixed models with participants modelled as random factors, using baseline measurements as a covariate. Analysis of language-based creativity tasks will additionally include fluency (as measured by the NIH Picture Vocabulary Test) as a covariate. EEG LTP and MMN data will be analysed consistent with Sumner et al. [53, 54]. fMRI data will be analysed for network connectivity, inter-network connectivity, and node-based connectivity, with an additional secondary analysis of seed-based functional connectivity of the left and right amygdala. Daily questionnaire VAS data will be analysed using a linear mixed effects model. Regression analyses of any significant effects will be undertaken with genetic biomarkers, baseline MODTAS scores, change in MODTAS scores, SoS/SoP, and fMRI baseline connectivity of the DMN as predictors. Expectancy effects will be assessed by regression analysis of measure scores to a corresponding construct on a baseline expectancy questionnaire (Table 4). Due to the use of multiple primary outcome measures, the Bonferroni-Holm step-down procedure will be employed to correct for multiple comparisons where appropriate. Secondary measures will be uncorrected but considered as exploratory.

**Table 4 Tab4:** Expectancy items and corresponding measures

Expectancy item	Measures
*Do you expect that microdosing will change how ____ you feel?*	
Angry	Anger VAS
Anxious	Anxiety VAS DASS Anxiety (−) DFlex BFI-2 Negative Emotionality
Calm	Calm VAS
Connected to others	Connected VAS NIH Toolbox Social Satisfaction Summary BFI-2 Agreeableness BFI-2 Conscientiousness BFI-2 Extraversion
Creative	Creative VAS AUT RAT CAT Everyday problem solving
Focused	Focus VAS
Guilty	Guilt VAS
Happy	Happy VAS NIH Toolbox Psychological Well-Being Summary
Meditative	FFMQ
Motivated	Motivated VAS
Open to new experiences	BFI-2 Open-Mindedness MODTAS State of Surrender (−) State of Preoccupation 5D-ASC
Sad	Sad VAS DASS Depression
Stressed	Stressed VAS PSS DASS Stress
Well	Well VAS (−) AEs Fitbit Sleep and Activity
*Do you expect that microdosing will change how ____ you feel?*	
Craving	Craving VAS
Energy	Energy VAS (−) Tired VAS Fitbit Sleep and Activity
Self-efficacy	NIH Self-Efficacy
*Do you expect that microdosing will affect your ___*	
Cognitive functioning	NIH Toolbox Fluid Cognition Composite Score

“−” indicates negative correlation is expected

An interim analysis will be undertaken at 6-month periods for review by the Data Safety and Monitoring Committee (DSMC; see the “Data and safety monitoring” section). Interim analyses include recruitment and dropout rates, demographics, data completion, attendance and compliance, comparison of outcome measure baseline means by group, summaries of daily mood VAS ratings and vital signs, summaries of adverse events, and comparison of adverse events between the groups (see the “Adverse event reporting and harms” section). The DSMC is able to terminate the trial based on these reports.

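### The stated 80% sensitivity (d = 0.56, r = 0.37, r = 0.27) counts every randomised participant; with the ten dropouts the plan leaves unreplaced, power for the day-43 contrasts and regressions is about 75%

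*Protocol article*

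**What the plan says.** All references are to the protocol article; no separate SAP was available.

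- **Size.** Study design describes an "inactive placebo-controlled parallel-group trial with 80 participants", allocated 1:1 in blocks of ten, so 40 per arm.
- **Sensitivity.** Statistical analyses and power calculations works "using *α* = 0.05, (1-*β*) = 0.8" and reports: "For independent sample *t* tests where *n* = 80, our trial will be sensitive to the effects where Cohen’s *d* = 0.56". It continues: "For linear regressions, *r =* 0.37 with *n* = 40 (single group) and *r* = 0.27 with *n* = 80 (combined groups". Whether the tests are one- or two-sided is not said.
- **Attrition.** The same paragraph adds: "Dropouts are anticipated; however, due to the novelty of the protocol, the rate cannot be estimated". Its only recruitment response is: "In the event that there are more than ten dropouts, an extra randomisation block of participants will be added to the study". The data from that block are assigned to the per-protocol analyses.
- **Routes to dropout.** Study design withdraws participants for, among other reasons, inadequate dose compliance, a serious adverse event, or a persistent adverse event that disrupts daily life. Strategies to improve adherence adds, about the dosing videos, that "those that fail to record repeatedly will be eliminated from the trial".
- **Missing data.** Sub-group data analysis and handling missing data plans per-protocol and intention-to-treat analyses, the latter with imputation, and a comparison of the two.
- **Timing of the primary measures.** Under Outcomes, the BFI-2, MODTAS and fMRI are taken at baseline and day 43 only. The AUT, RAT, LTP and MMN are also taken on day 1.

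**The concern.** The sensitivity statement is made about the trial, and its n is the whole randomised sample. That n supplies day-43 data only if nobody is lost, and the next sentences of the paragraph say losses are expected. Up to ten of them lead to no replacement.

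The article says there are no earlier effect sizes to power on, so these three figures are the only quantitative account of what 80 participants can show. A reader of a null day-43 result would naturally turn to them to judge which effects the trial was likely to have detected. If the n behind them is not reached, that reading is somewhat too favourable.

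**Working it through.** **Inputs.** Alpha 0.05, target power 0.80, n = 80 and n = 40, d = 0.56, r = 0.37 and r = 0.27, all from the power paragraph; 1:1 allocation from Study design; a threshold of more than ten dropouts from the power paragraph.

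**Step 1: reproduce the printed figures.** For the two-sample t test, the noncentrality is d·√(n₁n₂/(n₁+n₂)) on n₁+n₂−2 degrees of freedom. For a regression slope, it is √(n·r²/(1−r²)) on n−2 degrees of freedom.

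- t test, 40 v 40: 0.56·√20 = 2.504; the one-sided critical value is 1.665; power 79.9%. The effect at exactly 80% is d = 0.561.
- Regression, n = 40, r = 0.37: √(40 × 0.1369/0.8631) = 2.519; power 79.6%. The effect at 80% is r = 0.372.
- Regression, n = 80, r = 0.27: √(80 × 0.0729/0.9271) = 2.508; power 80.0%. The effect at 80% is r = 0.270.

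All three printed values are recovered one-sided. Two-sided, the detectable effects would be d = 0.634, r = 0.414 and r = 0.302, so none is recovered.

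**Step 2: apply ten unreplaced dropouts.** 80 − 10 = 70, or 35 per arm if losses are even.

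- t test, 35 v 35: 0.56·√17.5 = 2.343; critical value 1.668; power 75.0%.
- t test, 40 v 30 (all ten from one arm): 0.56·√(1200/70) = 2.319; power 74.2%.
- Regression, n = 35, r = 0.37: noncentrality 2.356; power 74.6%.
- Regression, n = 70, r = 0.27: noncentrality 2.346; power 75.1%.

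For fewer evenly split losses, one-sided power at d = 0.56 is 79.0% with 39 per arm, 78.0% with 38, 77.1% with 37 and 76.1% with 36.

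**Step 3: effects detectable with 80% power.**

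| Analysis | One-sided, no dropout | One-sided, ten lost | Two-sided, no dropout | Two-sided, ten lost |
|---|---|---|---|---|
| t test, n = 80 → 70 | d 0.56 | d 0.60 | d 0.63 | d 0.68 |
| Single group, n = 40 → 35 | r 0.37 | r 0.39 | r 0.41 | r 0.44 |
| Combined, n = 80 → 70 | r 0.27 | r 0.29 | r 0.30 | r 0.32 |

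The proportional loss hardly depends on sidedness: two-sided, power at d = 0.634 falls from 80% to 74.4%.

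**Step 4: what the replacement rule does.** Let D be the number of dropouts. Without the extra block, 80 − D participants complete. Once D exceeds ten, and if everyone in the extra block completes, the per-protocol count is at most 90 − D: 79 at D = 11, 70 at D = 20, 69 at D = 21 and 65 at D = 25. As written, the extra block does not enter the intention-to-treat analysis, where D = 11 leaves 80 − 11 = 69 observed. Seventy is therefore the count just before the rule acts, not its floor.

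**Step 5: possible offset from baseline adjustment.** A baseline covariate with correlation ρ to the outcome multiplies the residual variance by 1 − ρ². It cancels the fall from 80 to 70 when 1 − ρ² = 70/80, that is ρ = √0.125 = 0.35. The article gives no value of ρ.

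**The case against.** The strongest reply is that nothing printed is wrong. The calculation is conditional on a named n, and each figure reproduces at that n. The article discloses that dropouts are expected, explains why it gives no rate, and says how missing data will be handled. The framework is exploratory and d = 0.56 is not a target effect, so a detectable d of 0.60 overturns no design decision. Four of the seven primary measures also have a value in the acute phase of the supervised first dose, before home dosing begins, so participants removed over missed videos still contribute there. Questionnaires and creativity tasks are analysed with baseline as a covariate, not with the t test. And the unstated one-sided alpha matters more: two-sided power at d = 0.56 is 69.6% even with all 80.

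Much of this stands. A reader might infer an arithmetic error; there is none. Nor can the loss be spread evenly over every outcome: the day-1 contrasts would lose fewer participants, and for the baseline-adjusted outcomes a net loss is not shown.

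Three parts do not answer the point. An unknown dropout rate does not prevent a sensitivity figure, which needs an n rather than a forecast, and the plan's own threshold supplies one. Imputation does not in general restore lost information: on the BFI-2, MODTAS and fMRI a participant lost before day 43 has no post-baseline value. And settling sidedness would leave attrition untouched: two-sided power at d = 0.56 falls further, from 69.6% to 63.7%, with 35 per arm.

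**Conclusion.** The concern holds in a limited form. The three figures are right for 80 and 40 participants with outcome data, but the design does not secure those numbers at day 43 under attrition it expects and accepts without action. The cost is at most about five percentage points within the first ten evenly split dropouts: power at d = 0.56 lies between 75% and 80%, so the chance of missing that effect rises from 20% to as much as 25%. The size rests on the one-sided alpha implied by the printed figures, an even split of losses (74.2% if all ten leave one arm), and unadjusted analysis. It applies to the day-43 contrasts and the regressions.

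Two stronger readings are tempting. One is that 70 completers is what the trial should expect, or the worst it permits. The article gives no dropout rate, and beyond 20 dropouts even the per-protocol count falls below 70. The other is that the trial is too small and must recruit more. With no target effect in the article, the loss changes how the sensitivity should be described, not whether 80 is adequate.

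**What to change.** In Statistical analyses and power calculations:

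1. State that the n = 80 and n = 40 figures assume no dropout.
2. Give beside them the effects detectable with 80% power at ten unreplaced dropouts. On the one-sided basis the article implies, these are d = 0.60 (35 per arm), r = 0.39 (n = 35) and r = 0.29 (n = 70). If two-sided testing is intended, they are d = 0.68, r = 0.44 and r = 0.32, and the no-dropout figures become 0.63, 0.41 and 0.30. Name the sidedness.
3. Describe 70 as the count just before the extra block is triggered, not as an expected or minimum number.
4. Commit to reading null results against the number of participants who actually supplied outcome data for the contrast in question.

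The cost is a few sentences and a slightly less favourable stated sensitivity. Recruitment, visits and analysis methods do not change.
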